**Outcome:**

The two primary outcomes are the time needed to complete the obstacle subtask of the Emory functional ambulation profile (EFAP-obstacle) and the error-corrected time score on the walking adaptability ladder test (WALT). To correct for the two primary outcomes significant effects are assumed for *p* < 0.025. Secondary outcomes include lab-based tests to assess target stepping and gait stability and commonly used clinical tests to assess balance and walking capacity. Furthermore, home-based walking activity and falls are monitored.

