#### Primary outcomes

We include two primary outcome measures for evaluating walking adaptability, the obstacle avoidance subtask of the Emory functional ambulation profile (EFAP-obstacle) and the walking adaptability ladder test (WALT) [29, 30]. The EFAP-obstacle has previously been used as an outcome measure for walking adaptability in a stroke population [8], but is expected to show a ceiling effect in our research population of community ambulators [31]. Therefore, we additionally used the newly developed WALT, which has been shown to be responsive to walking adaptability training effects in adults with hereditary spastic paraplegia and in children with developmental disorders [32, 33], but has not yet been validated in PwS.

During the EFAP-obstacle, participants traverse a standardized 5 m obstacle course at a comfortable walking speed, including stepping over two boxes (10(l) × 100(w) × 5(h) cm) put on the floor, and turning around a chair without touching it. Time to complete the EFAP-obstacle task is the main outcome parameter.

The WALT consists of a 10 m agility ladder with 18 stepping targets, which progressively decrease in length (2 cm per target, ranging from 69 to 35 cm). Participants are instructed to walk back and forth over the ladder as fast and accurately as possible, in single and double run conditions. During the single run, one foot is placed in each target. During the double run, both feet are consecutively placed in each target. Accuracy is rated by counting the number of stepping errors (wrong number of feet per target, touching the borders of the target or jumping in double run). Each error results in a 1-s time penalty. Execution of the WALT is recorded by video, following the recommendation of Kuijpers et al. (2020) to ensure reliability [30]. The video recordings are used to identify errors, and to record the time needed to complete the WALT. The main outcome measure is the sum of the time needed to complete the WALT plus the time penalty.

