### Sample size

The sample size calculation was based on previous work comparing pre- to post-walking adaptability training intervention in a stroke population using the EFAP-obstacle (effect size: 0.7) [8]. Assuming a change of 10% of the intervention effect size in the waiting list control group, each group should include 47 participants to achieve a power of 80%, setting the alpha level at 0.025 to correct for two primary outcome measures. A correction factor was applied to account for a correlation (*r* = 0.5) between T0 and T1 [43], resulting in 35 participants per group. Taking 15% attrition into account, in total 84 participants will be randomized.

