### Statistical methods

To evaluate the effect of the training program, an intention-to-treat analysis will be conducted as the primary analysis. All participants who are randomized to one of the two study arms (including those who drop out during the intervention period, or never started the intervention) will be included in the primary analysis. In addition, a per-protocol analysis will be performed, excluding participants in the experimental group not completing the training program or participants in the waiting-list control group receiving training targeting walking adaptability. The training program is considered complete if at least 8 out of 10 training sessions are concluded.

The effect of the walking adaptability training on primary and secondary outcomes will be tested with a linear mixed model. The scores at post-intervention (T1) will be used as the dependent variable and group allocation (intervention or waiting-list control) as the independent variable; covariates are baseline scores of the dependent variable (T0) and the stratification variable (MI score), and participant ID as a random factor. A Bonferroni correction will be applied due to the two primary outcome measures; therefore significant effects are assumed for *p* < 0.025. Effects will be presented as the mean difference with 95% confidence intervals.

For the responder analysis, we will use the data of all participants who completed the training program in the study, because all participants underwent the walking adaptability training either as the experimental group or directly following the waiting-list period. To identify baseline participant characteristics that predict a response to training (defined as scores on the EFAP-obstacle or WALT), a linear regression model will be used. Predictors for response to the training will be collected during the intake assessment and T0 for both groups. To determine response to training, the relative change in EFAP-obstacle and WALT at T1 for the experimental group and T2 for the waiting-list control group will be used. Age, Motricity Index score and the miniBESTest score will be tested for their predictive value, and an exploratory analysis will be performed on other variables that may predict outcome.

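### Testing both primary outcomes at a fixed 0.025 is valid, but Holm's step-down test gives more power at the same familywise error of 0.05 and the same sample size

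*Protocol article*

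**What the plan says.** The protocol article has two primary outcomes, EFAP-obstacle time and the error-corrected WALT time: "We include two primary outcome measures for evaluating walking adaptability" (Primary outcomes).

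The rule for testing them is fixed in three places, and the three agree:

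- Statistical methods: "A Bonferroni correction will be applied due to the two primary outcome measures; therefore significant effects are assumed for" p < 0.025.
- Abstract, Outcome: "To correct for the two primary outcomes significant effects are assumed for" p < 0.025.
- Sample size: "setting the alpha level at 0.025 to correct for two primary outcome measures".

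No step-down or hierarchical rule is mentioned. The article does not say whether success means an effect on one primary outcome or on both. Effects are to be reported with 95% confidence intervals (Outcomes; Statistical methods).

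The article does not expect the two outcomes to be equally sensitive. Of EFAP-obstacle it says that it has been used before in stroke, "but is expected to show a ceiling effect in our research population of community ambulators". The Discussion expects WALT to be the more sensitive of the two. Primary outcomes adds that WALT has not yet been validated in people with stroke.

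**The concern.** Single-step Bonferroni holds the second outcome at 0.025 even after the first has been declared significant. For familywise control that is stricter than necessary. Once one null hypothesis has been rejected at 0.025, only one remains in a family of two, and Holm's procedure may test it at 0.05.

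The rules differ in one situation only: one primary p-value is below 0.025 and the other lies between 0.025 and 0.05. Suppose WALT is clearly significant and EFAP-obstacle has p = 0.03. Under the plan EFAP-obstacle is called non-significant, although its planned 95% interval would exclude zero. Under Holm it is significant and agrees with that interval.

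This matters because EFAP-obstacle is the only outcome with a stated basis for the sample size and WALT is not yet validated in this population. Support from EFAP-obstacle would strengthen a positive WALT result.

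**Working it through.** **Inputs from the protocol article (Sample size)**

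- Pre-post effect "in a stroke population using the EFAP-obstacle (effect size: 0.7").
- "Assuming a change of 10% of the intervention effect size in the waiting list control group": 0.10 × 0.7 = 0.07, so the between-group effect is d = 0.70 − 0.07 = 0.63.
- "each group should include 47 participants to achieve a power of 80"%, at alpha 0.025.
- Correlation of 0.5 between T0 and T1, 35 per group after correction, 15% attrition, 84 randomized.

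**Assumptions, because the document gives no figure**

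- Tests are two-sided. A two-sided 0.025 gives 48 per group and a one-sided 0.025 gives 40, so the stated 47 fits two-sided.
- WALT has the same effect as EFAP-obstacle (d = 0.63); a weaker case of d = 0.30 for one outcome is also shown.
- The correlation rho between the two test statistics is varied from 0 to 0.9.

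**Step 1: reproduce the plan's sample size.** n per group = 2 × [(2.2414 + 0.8416) / 0.63]² = 47.9, rounded up to 48, against the stated 47. The baseline correction is 1 − 0.5² = 0.75, and 47 × 0.75 = 35.25, or 35. Attrition: 35 / 0.85 = 41.2, rounded up to 42 per arm, 84 in total. The plan's figures reproduce within one participant per group before correction.

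**Step 2: power of a single test at 35 per arm.** Standard error = √0.75 × √(2/35) = 0.207; expected test statistic = 0.63 / 0.207 = 3.043.

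- At 0.025: Φ(3.043 − 2.241) = 78.9%.
- At 0.05: Φ(3.043 − 1.960) = 86.1%.

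**Step 3: compare the rules.** For each rho, 2,000,000 pairs of correlated normal test statistics were simulated with d = 0.63 on both outcomes.

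| rho | Per outcome, Bonferroni → Holm | Both, Bonferroni → Holm | At least one, either rule |
|---|---|---|---|
| 0 | 78.9% → 84.6% | 62.3% → 73.6% | 95.6% |
| 0.5 | 78.9% → 83.6% | 67.2% → 76.6% | 90.6% |
| 0.9 | 78.9% → 82.2% | 73.7% → 80.4% | 84.1% |

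The gain per outcome is 5.7, 4.7 and 3.3 points; the gain for both is 11.3, 9.4 and 6.7 points.

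The rho = 0 row can be checked by hand with p = 0.789 and q = 0.861. Holm per outcome is p + (q − p) × p = 0.789 + 0.072 × 0.789 = 0.846. Holm for both is q² − (q − p)² = 0.741 − 0.005 = 0.736.

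**Step 4: one weaker outcome.** With d = 0.30 on one outcome and 0.63 on the other, power for the weaker one rises from 21.4% to 28.6% (rho 0) or 30.4% (rho 0.9). The stronger one gains 0 to 1.6 points.

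**Step 5: error rates.** With no effect on either outcome, the familywise error is the same under both rules: 0.049, 0.047 and 0.036 at rho 0, 0.5 and 0.9. With a real effect (d = 0.63) on one outcome only, the false-positive risk on the null outcome is 0.025 under Bonferroni. Under Holm it is 0.045, 0.042 and 0.038 at the same correlations. At rho 0 this is 0.025 + 0.025 × 0.789 = 0.045.

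**The case against.** The strongest reply is that nothing here is wrong. The 0.025 threshold is stated consistently, controls the familywise error and matches the sample size. That stands, and it sets the weight of the point.

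Second, the Discussion reads as if WALT was added as insurance against an insensitive EFAP-obstacle. If an effect on either outcome is enough, Holm gains nothing, because the chance of at least one significant result is identical. This also stands. A reader might infer that the trial's overall chance of success rises by 7 to 11 points, but that would need a both-outcomes criterion, which the article does not state.

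Third, a reader might infer that the stricter rule buys nothing. It does buy something: Bonferroni holds each outcome's own false-positive risk at 0.025, whereas Holm lets it rise to about 0.04 to 0.045 when the other outcome has a real effect. That stays within the 0.05 familywise limit, which is the limit the correction is there to protect.

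Fourth, Bonferroni has simple matching 97.5% intervals and Holm has no equally simple simultaneous intervals. The plan reports 95% intervals, so it does not use this advantage. For the same reason, a worry that a 97.5% interval might include zero while Holm rejects does not apply to the intervals planned.

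Fifth, Holm does not cure a ceiling effect. In the d = 0.30 case, power for the weaker outcome stays near 30%.

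**Conclusion.** The point holds as an optional, low-cost improvement. The fixed 0.025 is valid, but less powerful than Holm's test at the same familywise error of 0.05. With 35 analysable participants per arm and d = 0.63 on both outcomes, the gain is about 3 to 6 points per outcome and 7 to 11 points for both, over correlations of 0 to 0.9. It is zero for at least one outcome.

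That Holm rejects whatever Bonferroni rejects, and controls the familywise error under any correlation, needs no assumption about this trial. The size of the gain does: it depends on the WALT effect and the EFAP-WALT correlation, neither of which the document gives.

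A reader might infer that the multiplicity control is faulty or the sample size wrong. The document supports neither: the threshold is coherent throughout and the sample size reproduces.

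**What to change.** Before unblinding, replace the Bonferroni sentence in Statistical methods, and the p < 0.025 threshold in the Abstract's Outcome paragraph, with:

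> Holm's procedure: the smaller of the two primary p-values is tested at 0.025 and, if significant, the other at 0.05; Holm-adjusted p-values will be reported.

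Keep the sample size at alpha 0.025. Under Holm no primary outcome is ever tested at a stricter level, so the calculation remains valid as the worst case.

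Show the adjusted p-values beside the planned 95% intervals. With p₁ the smaller and p₂ the larger p-value, these are 2p₁ and the larger of 2p₁ and p₂, each capped at 1 and compared with 0.05. They are needed because the 95% intervals are not simultaneous: if the smaller p-value lies between 0.025 and 0.05, its interval excludes zero although Holm rejects nothing.

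The costs are these:

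- An amendment notified to the ethics committee, as Regulation statement and ethics approval requires for all protocol changes. It should be dated before anyone has seen outcomes by arm, because participants are not blinded and the article describes blinding only for the assessor who scores the primary outcomes from video.
- The higher false-positive risk for a single null outcome given under working.
- No extra participants or data.

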### Outcomes

For all outcomes, the primary endpoint of this trial is the measurement at T1. The reported statistics will include mean group differences and the associated 95% confidence intervals, as well as group means with SD.

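### The two primary outcomes are tested at a two-sided 0.025 but reported with unlabelled 95% confidence intervals, so interval and verdict can disagree (minor reporting inconsistency)

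*Protocol article*

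**What the plan says.** The threshold for the primary outcomes appears in three places and is the same each time. Statistical methods: "A Bonferroni correction will be applied due to the two primary outcome measures; therefore significant effects are assumed for *p* < 0.025". The abstract, under Outcome: "To correct for the two primary outcomes significant effects are assumed for *p* < 0.025". Sample size: "each group should include 47 participants to achieve a power of 80%, setting the alpha level at 0.025 to correct for two primary outcome measures".

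The interval level appears in two places. Statistical methods, directly after the Bonferroni sentence: "Effects will be presented as the mean difference with 95% confidence intervals". Outcomes, in a paragraph that opens by covering all outcomes: "The reported statistics will include mean group differences and the associated 95% confidence intervals, as well as group means with SD". That paragraph therefore includes EFAP-obstacle and WALT.

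Nowhere does the article give a 97.5% or otherwise adjusted interval for the primary outcomes, and nowhere does it describe the 95% intervals as unadjusted or descriptive.

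**The concern.** A confidence interval and a two-sided test agree only when the confidence level is one minus the significance level. With 0.025 per outcome that level is 97.5%, whereas the plan fixes 95%. For p-values in the band from 0.025 up to 0.05, the report would show an interval clear of zero next to a statement that the effect is not significant, with no label to explain it.

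What is at stake is how the main result is read. The mean difference with its interval is the effect estimate the trial commits to publish, and many readers judge efficacy by whether the interval includes zero. The protocol sized the trial at 0.025 to allow for two primary outcomes. Unlabelled intervals at the uncorrected level invite readers to apply 0.05 instead.

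**Working it through.** **Inputs, all from the Sample size section unless noted**
- Pre-post effect size on EFAP-obstacle: 0.7.
- Control change: 10% of this, 0.07. Between-group difference: 0.7 − 0.07 = 0.63 SD.
- Alpha 0.025, power 80%, T0–T1 correlation r = 0.5, 47 then 35 per group, 15% attrition, 84 in total.
- Interval level 95% (Outcomes; Statistical methods).

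**Step 1. Is 0.025 one-sided or two-sided?** This decides the point, because a one-sided 0.025 test would match a two-sided 95% interval. The article does not state the sidedness in words, but its sample size shows it. Per group, n = 2 × ((z_alpha + z_power) / 0.63)², with z_power = 0.842:
- two-sided 0.025: 2 × ((2.241 + 0.842) / 0.63)² = 47.9
- one-sided 0.025: 2 × ((1.960 + 0.842) / 0.63)² = 39.6

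The stated 47 fits only the two-sided test. The rest of the plan's calculation follows: 47 × (1 − 0.5²) = 35.25, stated as 35; 35 / 0.85 = 41.2, rounded up to 42 per group, or 84.

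**Step 2. Width.** The half-width of a 95% interval is 1.960 SE. The half-width that matches two-sided 0.025 is 2.241 SE. Ratio: 2.241 / 1.960 = 1.144, so the matching interval is about 14% wider (about 15% with t quantiles at 66 to 81 degrees of freedom).

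**Step 3. The conflict band.** Test and interval disagree when the estimate lies between 1.960 and 2.241 SE from zero, that is, when 0.025 ≤ p < 0.05.

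**Step 4. Chance of landing in the band, for one outcome.** With 35 per group and r = 0.5, SE = √0.75 × √(2/35) = 0.207 SD, so the planned effect lies 0.63 / 0.207 = 3.04 SE from zero. The noncentral t uses 66 degrees of freedom (70 participants less four model terms: intercept, group, baseline score, Motricity Index).

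| True effect | Normal approximation | Noncentral t, 66 df |
|---|---|---|
| none | 2.5% | 2.5% |
| half of planned | 9.5% | 9.6% |
| three quarters of planned | 11.0% | 11.5% |
| planned (0.63 SD) | 7.2% | 7.9% |

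The t figure at the planned effect is the power at 0.05 minus the power at 0.025: 0.851 − 0.771, which is 0.079 before the two powers are rounded. The normal approximation peaks at about 11.2%, when the true effect is about 2.1 SE.

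**Step 5. An example.** Take an estimate of 2.1 SE = 0.435 SD, so p = 0.036, not significant under the plan.
- 95% interval: 0.435 ± 1.960 × 0.207 = 0.029 to 0.840, excludes zero.
- 97.5% interval: 0.435 ± 2.241 × 0.207 = −0.029 to 0.899, includes zero.

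**The case against.** The strongest reply is that nothing in the inference is wrong. Significance is defined by the p-value alone, no section makes the interval a decision criterion, and each 95% interval has valid 95% coverage for its own mean difference. Unadjusted 95% intervals are common and acceptable for estimation. The Outcomes section says what reported statistics will include, which does not bar an adjusted interval beside the 95% one. All of this stands, and it is why the point is minor.

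Two stronger readings are tempting, and the article supports neither.
- A reader might infer that the 95% intervals undo the multiplicity control. They do not: the p < 0.025 rule is intact, and familywise error stays at or below 0.05. A rate of up to 0.10 (0.0975 if the outcomes were independent) would arise only if someone ignored the stated rule and used the intervals as the tests.
- A reader might infer that the plan breaks a promise of joint 95% coverage. It makes no such promise; the correction is applied to significance only.

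It can also be said that a label is the kind of detail a condensed article leaves to a fuller document. That would answer a complaint about something missing. Here, however, the article itself fixes both the threshold and the interval level, and the two do not match.

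**Conclusion.** The point holds as a minor reporting inconsistency. The primary intervals are set at a level that does not match the two-sided 0.025 rule, and nothing labels them as unadjusted. The formal test, familywise type I error, power and sample size do not change.

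For one outcome, the chance of a visible conflict runs from 2.5% under no effect to about 11%, with about 8% at the planned effect. The 8% assumes a 0.63 SD difference, r = 0.5 and 35 analysed per group. It applies to EFAP-obstacle only, because the article gives no effect size for WALT; extending it to both primary outcomes would be an assumption. A true EFAP-obstacle effect somewhat below plan is credible on the article's own account, since the Primary outcomes section and the Discussion expect a ceiling effect, and a modest shortfall moves the chance towards the upper end of the range.

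**What to change.** In Outcomes and in Statistical methods, state that EFAP-obstacle and WALT are reported with 97.5% confidence intervals, matching the 0.025 threshold. These may stand alone or beside 95% intervals labelled as unadjusted for multiplicity and not used to judge significance. Keep 95% intervals for the secondary outcomes, labelled unadjusted. If the sponsor prefers to show only 95% intervals for the primary outcomes, the same label would remove the ambiguity, although the interval would still not mirror the test.

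The cost is one sentence in each section and primary intervals about 14% wider. No participants, data or procedures are added. The wording should be settled before results are known, so that the choice of interval cannot depend on them.

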The primary objective of this study is to evaluate the efficacy of walking adaptability training using an instrumented treadmill with augmented reality (C-mill) against usual care. The C-mill has been developed to incorporate the principle of task-specific training and to enable a high dose of walking practice per session, which are requirements for effective training [9, 15, 16]. We hypothesize that people receiving the walking adaptability training will improve their walking adaptability when compared to a waiting-list control group receiving usual care. As a secondary objective, we aim to conduct a responder analysis to explore potential determinants (e.g., age, disease severity and balance capacity) of treatment effects. Such insights are expected to inform tailored prescription for increasing the individual’s likelihood of benefitting from walking adaptability training [14].

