**Fig. 1 Fig1:**
[figure not shown]
Timeline for the study

After conducting all the assessments during T0, participants are randomized to either the experimental group or the waiting-list control group. Participants will then either train or wait for 5 weeks, followed by a second assessment (T1) within 1 week after this period. Assessments at T1 are equal to baseline assessments (T0) in combination with the home-based monitoring period. Following T1, the waiting-list control group will receive the same walking adaptability training as the experimental group. They will undergo an additional assessment (T2) after the training period, identical to T0 and T1 assessments, to be used for responder analysis. Participants will also fill in a short questionnaire every month from baseline onward to report falls in the preceding month.

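### The responder analysis estimates predictors of total change after training, not determinants of the training effect as the secondary objective asks; a randomized group-by-predictor interaction should be added

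*Protocol article*

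**What the plan says.** The Background and rationale section states the secondary objective: "we aim to conduct a responder analysis to explore potential determinants (e.g., age, disease severity and balance capacity) of treatment effects". It also states the use: "Such insights are expected to inform tailored prescription for increasing the individual’s likelihood of benefitting from walking adaptability training". The Discussion likewise expects the analysis to show who is most likely to benefit.

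The Statistical methods section fixes the analysis:

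- **Population:** "For the responder analysis, we will use the data of all participants who completed the training program in the study". This pools both arms, because the controls train after their waiting period.
- **Response:** "the relative change in EFAP-obstacle and WALT at T1 for the experimental group and T2 for the waiting-list control group will be used".
- **Model:** linear regression on baseline characteristics. No untrained comparator and no interaction with group is named.
- **Predictors:** "Age, Motricity Index score and the miniBESTest score will be tested for their predictive value", with other variables explored. On timing: "Predictors for response to the training will be collected during the intake assessment and T0 for both groups".

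The Participant timeline section gives the purpose of the extra control visit: "They will undergo an additional assessment (T2) after the training period, identical to T0 and T1 assessments, to be used for responder analysis". Under the same section both arms are assessed at T0 and T1, before the controls train. That randomized comparison is used for efficacy but has no stated role in the responder analysis.

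**The concern.** A determinant of the treatment effect is a trait across which the difference between training and no training varies. The planned regression has no untrained side, so it cannot separate that difference from change that would have occurred anyway. The two quantities coincide only if the other parts of the change score are unrelated to the trait. The article neither states that assumption nor plans to check it with the controls' T0-T1 change.

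The stake is the stated use. If a trait that is merely prognostic, or merely linked to the baseline measurement, is reported as a determinant of benefit, it could steer who is offered training.

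**Working it through.** **1. The plan's own figures (Sample size section).** Effect size 0.7; controls assumed to change by 10% of it, 0.07; between-group effect 0.7 × 0.9 = 0.63 SD. With two-sided alpha 0.025 and 80% power, n = 2 × ((2.241 + 0.842)/0.63)² = 47.9 per group, against 47 stated. Multiplying by 1 − r² = 0.75 gives 47 × 0.75 = 35.25, stated as 35. Then 35/0.85 = 41.2, so 42 per group and 84 in total. The figures reproduce to within one participant. No figure is given for the responder analysis.

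**2. What the change score contains.** Write change = training effect + untrained change + (post error − pre error). With equal variances and r = 0.5, the SD of change without any training is √(2(1 − 0.5)) = 1 baseline SD, and its correlation with the baseline score is −(1 − 0.5)/1 = −0.5. Individual change is thus large relative to a 0.63 SD effect and strongly tied to baseline. A trait's slope on relative change collects:

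- modification of the training effect, which is the target;
- any dependence of untrained or retest change on the trait;
- any sharing of same-day state with the baseline score;
- the effect of dividing by baseline.

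In the randomized T1 model, the group-by-trait coefficient keeps only the first, on the scale analysed, because the others are alike in both arms.

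**3. Simulated size.** Taken from the plan: 35 per arm, r = 0.5, effect 0.63, mean control change 0.07. Assumed: the trait's relations to baseline and to untrained change, the same-day loading, baseline CV (0.3; for same-day state 0.2 and 0.3), and r = 0.8 as an alternative. The training effect is constant in absolute units, so no trait modifies it. Change for the waiting-list group was counted from T0 in the runs without same-day state. Each row rests on 3,000 to 4,000 trials at a nominal 5%.

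| Assumption | Planned regression | Interaction |
|---|---|---|
| Trait unrelated to baseline, r = 0.5 | 5% | 5% |
| Trait-baseline correlation −0.3 / −0.5, r = 0.5 | 8% / 13% | 5% / 6% |
| Trait-baseline correlation −0.3 / −0.5, r = 0.8 | 13% / 32% | 5% / 5% |
| Same-day loading 0 / 0.2 / 0.35, r = 0.5 | 6-7% / 12-14% / 33-37% | 4-5% |
| Untrained change varying with trait by 0.1 / 0.2 / 0.3 SD per SD, r = 0.5 | 13% / 35% / 66% | 4-5% |

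Repeat runs with slightly different settings gave 6% / 13% for the second row, 12% / 26% for the third, and 27% for same-day loading 0.35. The mechanisms can also offset each other: with correlation −0.5 and an untrained slope of 0.1, the rate was 8%.

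**4. Dependence on scale.** If the effect is instead a constant proportion of baseline, the planned regression rejected in 7% / 9% of trials for trait-baseline correlations of 0.3 / 0.5, at both values of r. The raw-scale interaction rejected in 6% / 7% (r = 0.5) and 6% / 10% (r = 0.8).

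**5. Power.** For true modification of 0.2 / 0.3 / 0.4 / 0.5 / 0.6 SD per SD, the interaction has about 15 / 27 / 45 / 61 / 79% power at r = 0.5. At r = 0.8 it has 26 / 53 / 76 / 91% for the first four. When untrained change is unrelated to the trait, the planned regression detects 0.2 / 0.3 / 0.4 in about 35 / 64 / 86% at r = 0.5.

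**The case against.** The article calls this an exploratory search for potential determinants, explains why it pools all trained participants, and schedules T2 for that purpose. Participants are more than 6 months after stroke, the sample size allows only 0.07 SD of mean change in controls, and the Discussion expects controls to stay unchanged. Relative change is a defensible scale for timed tests, and the planned regression is considerably more powerful than an interaction. The mismatch could also be closed by rewording the objective.

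Much of this stands. It limits the size of the problem and rules out discarding the planned regression. It does not remove the mismatch: an unchanged group mean does not show that individual change is unrelated to a trait, and greater power for a different quantity does not answer the stated objective.

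A reader might infer more than the document supports:

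- **That a third or more of null traits will be flagged.** The 33-37% needs an assumed same-day loading of 0.35. Among the named predictors only the miniBESTest could show it: age has no same-day state, and the Motricity Index is taken at intake, about two weeks before T0. The 66% needs an untrained slope of 0.3 SD per SD, for which nothing in the article gives a basis.
- **That change to T2 is wrongly counted from T0, or that a group term is ruled out.** Neither is stated. A condensed article may leave both to the full protocol or analysis plan, so they are points to settle, not errors.
- **That the interaction is free of bias on any scale.** Step 4 of the working shows otherwise.

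**Conclusion.** The concern holds as a mismatch between objective and analysis. Carried out as written, the responder analysis identifies predictors of total change after training. Calling them determinants of the treatment effect requires an assumption the article does not make.

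The consequence ranges from slight (about 6-8% false positives at a nominal 5%) to material (roughly 10-35%), depending on how strongly a trait is tied to baseline and, for the miniBESTest, on shared same-day state. Those inputs are assumptions, as is an effect constant in absolute units; under a proportional effect much of the excess disappears. Trait-related untrained change could push the rate higher, but its size is unknown. The direction is firm, the magnitude is not. The analysis is secondary, and the primary efficacy conclusion does not depend on it.

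**What to change.** 1. Add group-by-predictor interactions for age, Motricity Index and miniBESTest to the randomized T1 model, adjusted for the T0 score and Motricity Index, for both primary outcomes and in all randomized participants. Report them as exploratory estimates with confidence intervals, and also on the relative (log) scale if the effect is thought proportional. Base any statement about determinants of the treatment effect on these.
2. Keep the pooled regression, but describe its results as predictors of change after training. State that T1 is the waiting-list group's pre-training reference, and include a group term. The article's own botulinum toxin timetable fits this reference: T1 to T2 in the waiting-list arm falls at the same times after injection as T0 to T1 in the experimental arm.
3. If the interactions are not added, reword the secondary objective and the Discussion to speak of predictors of change after training.

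The cost is a few model terms on data already planned, with no extra visits. The drawback is the low power shown above, so wide intervals must be expected and a null interaction must not be read as absence of effect modification. This is why the interaction supplements the planned regression and does not replace it.
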